#### Physical activity level and sedentary behaviour

To verify the physical activity level and sedentary behaviour, an accelerometry system will be used, using the activPAL3TM actigraph (PAL Technologies Ltd., Glasgow, UK) at assessment moments T1 and T2. The participant will receive guidance and will be instructed to use the monitor continuously for a week. The accelerometer data are transferred via a USB interface to the specific software activPAL version 8.11.6.70, which analyses data and estimates energy expenditure in MET/hour. This variable will be expressed as the average activity per day, excluding days that do not register the full 24 h.

The means of transference from sitting to standing during each day will also be presented, as well as the time spent in each posture. Sedentary behaviour will be defined by the time spent per day in sitting and lying postures in the waking period. In addition, the walking time, number of steps/day and cadence of steps will be calculated.

#### Life-Space Assessment

To verify the confinement adopted by participants, the Life-Space Assessment (LSA) questionnaire [36], translated and validated version for the Brazilian population, will be used [37]. The Brazilian translated and validated version showed adequate reproducibility (internal consistency of 0.92, reliability with ICC of 0.97 (95% CI: 0.95 to 0.98), standard error of measurement: 4.12 points—3%) [37].

### Plans to promote participant retention and complete follow-up {18b}

For participant retention and complete follow-up, the team of physiotherapists and physical educators responsible for the multicomponent training will make motivational conversations during the exercises and reinforce the importance of the study programme and evaluations. As this is a preexisting physical activity programme, the possibility of continuing in the programme after the end of the study is expected to motivate participants. In addition, participants will receive reports with individual feedback on test performance and leaflets to highlight the importance of each activity developed in the study.

### Data management {19}

Data collection will be performed by certified physiotherapists/researchers for all tests performed. Data will be stored on paper (source documents) within each participant’s medical records. The documents will be archived in a specific storage room at the Laboratory of Research in Health of Older Adults (LAPESI) of the Federal University of São Carlos, with restricted access to researchers. Data entry will be performed by two PhD students ([name] and [name]) from the research team (double-check). The data will be stored in Microsoft repositories, and the detailed data management plan will be carried out by the DMP tool platform. The data management plan is available from the corresponding author upon request.

### Confidentiality {27}

All sensitive data of participants will be archived in a repository of the Institution following the GDPR. Each participant will receive a numerical code, and personal data will be obliterated in the analysis.

### Plans for collection, laboratory evaluation and storage of biological specimens for genetic or molecular analysis in this trial/future use {33}

As seen in the “Additional consent provisions for the collection and use of participant data and biological specimens {26b}” section above, no biological specimens will be collected.

## Statistical methods

### Statistical methods for primary and secondary outcomes {20a}

Descriptive statistics for all variables will be obtained. Initially, the Shapiro–Wilk test will be used to verify the normality of the data distribution. The paired *t* test or Wilcoxon test will be used to assess changes in physical capacity on confinement, contrasting T0 and T1.

Regarding the intervention, to compare participant characteristics (age, years of study, MMSE and body composition) between groups at T0, the independent *t* test or Mann–Whitney test will be used, respectively, with or without normality of the data. Two-way ANOVA with repeated measures will be applied to assess the effect of interventions between groups and moments (T1 and T2) on functionality, quality of life, physical capacity, mental health, physical activity levels, life space, body composition and sedentary behaviour. The effect size will be calculated by eta partial square (ηp2), and values of 0.02, 0.06 and 0.14 will be considered small, medium and large effects, respectively [38]. The results will be presented in confidence intervals, and the analysis will be conducted according to intention to treat. If any participant presents with a COVID-19 diagnosis, a linear regression will be performed to verify the contribution of these data to the results obtained.

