## Abstract

**Background:**

Considering the confinement recommended by the World Health Organization due to the pandemic caused by COVID-19, many community physical exercise programmes for older adults have had their activities cancelled. In this context, proposing strategies to recover the possible adverse effects of the confinement period is pertinent. The use of self-management strategies associated with regular physical activity reduces sedentary behaviour and improves physical capacity in older adults. Thus, the purpose of this study was to describe a multicomponent training programme combined with a self-management strategy protocol to mitigate the effects of interruptions in physical exercise programmes on functionality, physical capacity, mental health, body composition and quality of life in older adults.

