**Methods:**

This will be a blinded, randomized and controlled clinical trial performed in São Carlos, SP, Brazil. Eighty older adults will be divided into two groups: multicomponent training (Multi) and multicomponent training + self-management strategies (Multi+SM). The intervention will be performed over 16 weeks on three alternate days of every week, with 50-min sessions. The assessment of physical capacity will be performed before the interruption of physical exercise programmes (T0: initial assessment, March 2020), preintervention (T1: immediately after the return of the exercise programme) and postintervention (T2). The assessments of physical activity level, quality of life, mental health, functionality and body composition will be performed at T1 and T2.

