### Objectives {7}

The present study protocol aims to describe the design and methods to mitigate the effects of interruptions in physical exercise programmes in the pandemic context on functionality, sedentary behaviour, physical capacity, mental health, body composition and quality of life in older adults using self-management strategies and multicomponent training.

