## Interventions

### Explanation for the choice of comparators {6b}

It is already known in the literature that multicomponent physical exercise has benefits for the physical and mental health of older adults. Thus, to evaluate whether the association of SMS with multicomponent exercises can be a good strategy to mitigate the negative outcomes of the social distance period for this population, the Multi group will be considered a control group for comparing the effect of the inclusion of these techniques with the Multi+SM group.

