### Outcomes {12}

For this study, the physical activity level and sedentary behaviour are considered the primary outcomes. These variables will be assessed by the energy expenditure (MET/hour), number of steps, cadence, transferences and the spent in each posture preintervention (T1: immediately after the return of the exercise programme) and postintervention (T2).

Secondary outcomes will be verified: (a) body composition in terms of lean mass and relative muscle mass; (b) functionality through an evaluation of cognition, mobility, self-care, interpersonal relationships, living and household activities and participation; (c) physical capacity according to a timed up and go test (time), handgrip strength, MMII strength, balance and 6-min walk test (distance walked); (d) mental health according to depressive symptoms and stress perception; (e) mobility according to a Life-Space Assessment; and (f) quality of life through a structured questionnaire. The outcomes are detailed in Table 2, and the plans for the assessment and collection of outcomes are described in the “Plans for assessment and collection of outcomes {18a}” section.

**Table 2 Tab2:** Overview of outcomes, outcome measures, instruments and assessment time

Outcomes	Outcome measures	Instrument	Assessment time
Personal information	Age, sex, educational background and medical conditions	Self-reported	T0, T1, T2
Body mass index	Height and weight	Stadiometer/weighing scale	T0, T1, T2
Body composition	Lean mass and relative muscle mass	Dual-energy X-ray absorptiometry	T1, T2
Functionality	Cognition, mobility, self-care, interpersonal relationships, living and household activities and participation	WHODAS 2.0	T1, T2
Physical capacity	Timed Up and Go (time); handgrip strength; MMII strength; balance and 6-min walk test (distance walked)	Timed Up and Go (TUG); manual dynamometer; 30-s sit and stand test; unipodal test; and 6-min walk test	T0, T1, T2
Mental health	Depressive symptoms and stress perception	Geriatric Depression Scale—GSD-15, and Perceived Stress Scale (PSS-10)	T1, T2
Physical activity level and sedentary behaviour	Energy expenditure (MET/h), number of steps, cadence, transferences, and the time spent in sitting and lying postures in the waking period	Accelerometry system activPAL3TM actigraph (PAL Technologies Ltd., Glasgow, UK)	T1, T2
Mobility	Life space	Life-Space Assessment (LSA)	T1, T2
Quality of life	Quality of life	WHOQOL	T1, T2

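### For physical capacity, T2 is never compared with the pre-interruption value: the deficit left at T2 has no planned estimate with a confidence interval, and T0 goes unused in the comparison of arms

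*Protocol article*

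**What the plan says.** All places are in the protocol article.

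- **Framing.** The abstract's Background says that "proposing strategies to recover the possible adverse effects of the confinement period is pertinent". Objectives {7} says that the protocol "aims to describe the design and methods to mitigate the effects of interruptions in physical exercise programmes in the pandemic context".
- **Randomised question.** In section {6b}, "the Multi group will be considered a control group for comparing the effect of the inclusion of these techniques with the Multi+SM group". Under Trial design {8}, randomisation takes place after the interruption period.
- **Measurement times.** The abstract's Methods says "The assessment of physical capacity will be performed before the interruption of physical exercise programmes (T0: initial assessment, March 2020"), followed by T1 and T2. Table 2 confirms all three visits for the Timed Up and Go, handgrip, 30-s sit and stand, unipodal and 6-min walk tests. Body mass index is also listed at T0. For the rest, "The assessments of physical activity level, quality of life, mental health, functionality and body composition will be performed at T1 and T2"; Table 2 gives the same two visits for life space.
- **Primary outcomes.** Outcomes {12} states that "the physical activity level and sedentary behaviour are considered the primary outcomes". They have no T0 value.
- **Analysis.** Section {20a} plans a paired t or Wilcoxon test that "will be used to assess changes in physical capacity on confinement, contrasting T0 and T1". For the intervention, "Two-way ANOVA with repeated measures will be applied to assess the effect of interventions between groups and moments (T1 and T2"). Section {20a} also names T0 when comparing participant characteristics between groups, but that is not an outcome analysis. Section {20b} excludes additional and subgroup analyses.

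**The concern.** Physical capacity is the one efficacy domain in which the loss during the interruption and the later gain can both be measured. The plan asks whether capacity fell (T0 to T1) and whether it changed afterwards (T1 to T2), and it does not join the two. An arm can gain clearly from T1 to T2 and still sit well below T0, or gain among people who had lost little.

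What is at stake is the conclusion. A significant T1-T2 gain could be reported as making good the interruption loss, with no interval for what is still missing. In addition, T0 was recorded before randomisation and probably predicts T2, yet the comparison of arms does not use it.

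**Working it through.** **1. What each planned analysis can show for physical capacity**

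| Contrast | Planned? | What it answers |
|---|---|---|
| T1 - T0 | Yes, paired test | Loss during the interruption |
| T2 - T1, by arm and between arms | Yes, group x time ANOVA | Change after resumption; added effect of SM |
| T2 - T0 | No | Deficit left at T2 |

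**2. Is the arm comparison invalid without T0?** No. Write D for the Multi+SM minus Multi difference. Then

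D(T2 - T0) = D(T2 - T1) + D(T1 - T0).

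The last term lies wholly before randomisation, so its expectation is zero. The planned T1-T2 interaction therefore already targets whether more is regained with SM.

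**3. Can a T1-T2 gain separate full from partial recovery?** This is an illustration with assumed values: unit SD at each visit, correlation 0.7 between visits, a T1-T2 gain of 0.4 SD, and 32 analysed in one arm (80 planned x 80% follow-up = 64, or 32 per arm). The SD of change is sqrt(2 x (1 - 0.7)) = 0.775, so the standardised gain is 0.4/0.775 = 0.52. Simulation with 4,000 replicates, two-sided 5%:

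| Assumed T0-T1 loss | Position at T2 relative to T0 | Power of paired T1-T2 test | T2 below T0 detected by paired T0-T2 test |
|---|---|---|---|
| 0.2 SD | +0.2 SD | 80% | 0.1% |
| 0.4 SD | 0 | 81% | 2.5% |
| 0.8 SD | -0.4 SD | 82% | 80% |

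The T1-T2 result is the same, apart from simulation noise, in all three cases. The ANOVA's time effect pools the two arms. It has more power but is equally blind to T0.

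**4. How precise would a T2-T0 estimate be?** The half-width of the 95% CI is t(0.975, n-1)/sqrt(n), in units of the SD of the T2-T0 difference. The last column is the shortfall detectable with 80% power at two-sided 5%, in the same units.

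| n per arm | Origin | Half-width | Detectable shortfall |
|---|---|---|---|
| 24 | 60 x 0.8 / 2 | 0.42 | 0.60 |
| 30 | 60 / 2 | 0.37 | 0.53 |
| 32 | 80 x 0.8 / 2 | 0.36 | 0.51 |
| 40 | 80 / 2 | 0.32 | 0.45 |

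A shortfall of up to about half an SD could easily be missed, so a non-significant T2-T0 difference would not show recovery.

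**5. What would T0 add to the arm comparison?** The document gives no correlations, so these are assumed, with equal SDs. Residual variance given T1 is 1 - r12². Given T1 and T0 it is 1 - R², where R² = (r12² + r02² - 2·r12·r02·r01)/(1 - r01²). The planned interaction with two visits is equivalent to comparing change scores, whose variance is 2(1 - r12).

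| r12, r02, r01 | Change score | T1 only | T1 and T0 | Cut from adding T0 to T1 | Cut against change score |
|---|---|---|---|---|---|
| 0.8, 0.7, 0.7 | 0.400 | 0.360 | 0.322 | 10.7% | 19.6% |
| 0.7, 0.6, 0.6 | 0.600 | 0.510 | 0.459 | 9.9% | 23.4% |
| 0.7, 0.7, 0.7 | 0.600 | 0.510 | 0.424 | 17.0% | 29.4% |
| 0.8, 0.6, 0.7 | 0.400 | 0.360 | 0.357 | 0.9% | 10.8% |

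Much of the last column comes from adjusting for T1 instead of using change: 10% at r12 = 0.8 and 15% at r12 = 0.7. Only the fifth column is due to T0.

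**The case against.** The strongest reply is that the trial never promised a return to T0. The title and objective speak of mitigating, and regaining half a loss is mitigation. Recovery appears only in rationale wording. The Discussion names the intervention effect, compared at T1 and T2, as the main objective, and it openly lists the missing T0 data for accelerometry, body composition, functionality and quality of life. All of that stands. A reader might infer that the trial fails to test its own aim, or that it cannot tell whether SM helps people regain more. The documents do not support either reading. Return to T0 is nowhere set as an objective or endpoint, and because randomisation follows the interruption, the T1-T2 interaction tests the SM question.

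A second reply is that a within-arm T2-T0 contrast is uncontrolled. T0 is March 2020 and recruitment began on 29 November 2021. That is about 20 months, and 16 weeks of intervention bring it to roughly two years or more, during which ageing and intercurrent illness act as well. This also stands. The contrast can describe what remains, but it cannot be the sole basis for a claim of mitigation.

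Third, descriptive statistics for all variables are promised, so the T0, T1 and T2 means would let a reader see the shortfall. That is true of the point estimate only; no interval for the difference is planned. Nor can the gap simply be put down to a separate analysis plan, because section {20a} fixes the visits and section {20b} excludes further analyses.

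**Conclusion.** The point holds within a narrow scope. For the five physical capacity tests, no planned analysis compares T2 with T0, so the remaining deficit is left without an interval, and T0 is not used to sharpen the arm comparison. The primary outcomes are unaffected because they have no T0 value, and the randomised comparison remains valid. This is a worthwhile improvement to a secondary analysis and to the wording of conclusions. It is not a flaw in the main test.

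The size rests on assumptions. Under correlations of 0.6 to 0.8, T0 beside T1 saves about 1% to 17% of residual variance, and adjusting for both saves about 11% to 29% against the planned change-type ANOVA. The 95% CI for T2 minus T0 in one arm would have a half-width of 0.32 to 0.42 SD of the difference. That is useful as description, but too wide for a non-significant result to be read as recovery.

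**What to change.** For physical capacity only:

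1. Add a secondary, descriptive estimate of T2 minus T0 by arm with a 95% CI. Label it as uncontrolled and as including ageing and intercurrent events since March 2020. State in advance that a non-significant difference will not be read as recovery.
2. Compare the arms at T2 with the T1 and T0 values as covariates. This is for precision; it targets the same arm effect and says nothing by itself about return to T0.
3. Word T1-T2 results as improvement after resumption, or as the effect of adding SM. Describe how much of the interruption loss was recovered only alongside the T2-T0 estimate.

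Reconcile section {20b} so that it does not exclude item 1. The cost is slightly more analysis and some missing T0 values, which the multiple imputation already planned in section {20c} can handle. No visit, participant or primary analysis changes.

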### Interim analyses {21b}

For this protocol, interim analyses are not needed because this is a low-risk intervention and it is not required by the ethics committee and regulatory authorities.

### Methods for additional analyses (e.g. subgroup analyses) {20b}

No additional or subgroup analyses will be performed as part of this trial.

### Methods in the analysis to handle protocol nonadherence and any statistical methods to handle missing data {20c}

The analysis to handle protocol nonadherence will follow the intention-to-treat analysis principles (HOLLIS et al., 1999), with missing data processed by a multiple imputation method. Participants who do not complete the intervention but who perform at least 70% of the sessions will be included in the statistical analysis by intention to treat.

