### Intervention description {11a}

Both groups will start the protocol activities after the return of physical exercise programmes. For this, the participants will be invited to a meeting, and they will receive information about sedentary behaviour. At the end of the meeting, informative material with these topics will be offered.

Multicomponent training will be performed by the Multi and Multi+SM groups. The design of the programme follows the American College of Sports Medicine (ACSM) recommendations and considers the previous physical exercise programme, combining muscular strengthening, flexibility and balance exercises [6]. A 16-week training protocol will be performed on three alternate days every week, with 50-min sessions (Table 1). During the sessions, all participants will use a heart rate monitor (Polar® H10) to monitor HR values and the exercise intensity. The SMS will be performed only by the Multi+SM group. If the intervention programme is effective for the Multi+SM group, the Multi group will also be invited to participate in SM strategies after the end of the study.

**Table 1 Tab1:** Multicomponent training

Training component	Exercise	Intensity	Progression
Warm-up (10’)	Walk and exercises with music and a ball	Increased progressively at moderate-to-vigorous intensity (according to each individual’s fitness levels)	The progression will be performed by the BORG scale, and activities with moderate intensity will be considered from 4 to 6 points and intense activity as 7–9 points
Balance (10’)	Walk in tandem, and dynamic balance circuits of direction and speed and surface changes	--	Progressive difficulty as tolerated and the progression of these exercises will be performed in relation to the support base, walk in circles and change of direction with increased speed
Muscular strengthening (20’)	Strengthening for the upper limbs, calf exercises; lunges; sit-ups; squats; step up and step down	1–3 sets of 8–12 repetitions, major muscle groups	The exercises load will progress according to the individual's suitability for the initial load
Flexibility/cool down (10’)	Stretching of major muscle groups and breathing exercises	30–60 s of static stretching	--

Adapted from Buto et. al., 2009 [25]

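### Section {20c} promises intention to treat with multiple imputation, then ties non-completers' inclusion to 70% attendance, which implies that those below it are left out

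*Protocol article*

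**What the plan says.** Three statements in the protocol article bear on who is analysed.

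- **Statistical methods for primary and secondary outcomes {20a}:** after describing the two-way repeated-measures ANOVA on T1 and T2, the article says "the analysis will be conducted according to intention to treat". That model covers every outcome listed there, including the primary ones; under Outcomes {12}, "the physical activity level and sedentary behaviour are considered the primary outcomes".
- **Nonadherence and missing data {20c}, first sentence:** nonadherence is to follow intention-to-treat principles, with "missing data processed by a multiple imputation method". No attendance condition is attached.
- **The same section, second sentence:** this one is about non-completers, and it says that those "who perform at least 70% of the sessions will be included in the statistical analysis by intention to treat".

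No other section says what happens to randomised participants who stop early with less than 70% attendance. No per-protocol or modified intention-to-treat set is named, and {20b} rules out additional analyses.

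**The concern.** An inclusion threshold on attendance does not fit an analysis that includes everyone randomised. If it is applied, people leave the primary comparison because of something they did after randomisation, and the two groups compared are no longer the two groups randomised.

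This matters here for three reasons.

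- Participants and therapists know the allocation ({17b}). Only the Multi+SM arm receives the diary, the pedometer and the weekly calls (Self-management strategies, under {11a}), so attendance could differ by arm. Added burden could lower it; added encouragement could raise it.
- The primary outcomes are physical activity and sedentary behaviour. Willingness to attend exercise classes is plausibly related to both.
- People who stop early are the most likely to lack a T2 measurement. Leaving them out narrows the work that the promised imputation would do.

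The article would nevertheless report the result as intention to treat.

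**Working it through.** **1. What the threshold means.** From {11a}: "A 16-week training protocol will be performed on three alternate days every week, with 50-min sessions". That is 16 × 3 = 48 sessions, and 0.70 × 48 = 33.6, so a non-completer needs at least 34. {11a} uses the word sessions for the multicomponent classes; {20c} does not say whether self-management contacts also count.

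**2. Does the second sentence of {20c} have a use under each reading?**

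| Reading | Non-completers at 70% or more | Non-completers below 70% | Effect of the sentence |
|---|---|---|---|
| All randomised are analysed ({20a}; first sentence of {20c}) | included | included | none; the 70% is redundant |
| Inclusion depends on 70% (second sentence of {20c}) | included | left out | defines the analysis set |

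The sentence does something only under the second reading, and that reading conflicts with {20a} and with the sentence before it. It cannot be taken to describe a separate sensitivity analysis, because {20c} calls it the intention-to-treat analysis and {20b} allows no additional ones.

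**3. How large could the bias be?** The plan has no figure for this to reproduce. The following is an illustration on assumed inputs; only the SD comes from the document.

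- SD of change in sitting time: 8.3% (Sample size {14}).
- Assumed: no true effect; a standard normal attendance propensity whose correlation *r* with the change in sitting time is 0.3 to 0.5; within each arm, those with the lowest propensity are left out.
- If a fraction *p* of an arm is retained, the mean propensity among those retained is m(p) = φ(z) / p, where z is the (1 − p) quantile and φ the density of the standard normal.
- Bias = r × 8.3 × [m(p₁) − m(p₀)].

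Values of m: m(0.90) = 0.1755 / 0.90 = 0.195; m(0.80) = 0.2800 / 0.80 = 0.350; m(0.60) = 0.3863 / 0.60 = 0.644.

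| Retained in the two arms | Difference in m | Bias at r = 0.3 | Bias at r = 0.5 |
|---|---|---|---|
| 80% and 80% | 0 | 0 | 0 |
| 90% and 80% | 0.155 | 0.3 × 8.3 × 0.155 = 0.39 | 0.5 × 8.3 × 0.155 = 0.64 |
| 80% and 60% | 0.294 | 0.3 × 8.3 × 0.294 = 0.73 | 0.5 × 8.3 × 0.294 = 1.22 |

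The sign depends on which arm loses more people and on the sign of the correlation. The zero in the first row holds because the model lets selection work in the same way in both arms. As {14} states no target difference, these values cannot be set against the effect that the trial was sized to detect.

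**The case against.** **Exclusion is not written.** {20c} contains neither an *only* nor an *excluded*, and both {20a} and the sentence before promise intention to treat without a condition. This stands. A reader might infer that the protocol openly removes low attenders, but it does not. What can be said is that the text contradicts itself and implies exclusion. An analyst who followed it could drop these people and still report intention to treat.

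**It is not a full per-protocol rule.** The threshold concerns non-completers. Nothing removes completers with low attendance or moves anyone between arms. This also stands; modified intention to treat is the closer description.

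**Imputation keeps a role.** A reader might infer that the rule leaves nothing to impute. In fact imputation would still serve non-completers at 70% or more without T2, completers who miss T2, and participants without usable accelerometer data. Its role is narrowed, no more.

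**Attendance may not differ by arm.** The classes are the same for both arms, and neither the adherence calls in {11c} nor the retention measures in {18b} are described as arm-specific. This is fair, and it is why the range starts at zero. It gives no assurance of equality.

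**Power.** A reader might infer that the rule costs participants beyond the 20% loss assumed in {14}. The documents do not support this. Early drop-outs may be the same people already counted in that 20%. The abstract also speaks of eighty participants where {14} has 60: losing 30% of 40 per arm leaves 28, against 24 per arm after a 20% loss from 30. No claim about power is made.

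**The trial is called exploratory ({8}).** True, but that does not make the label on the analysis correct.

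**Conclusion.** Wrong as written. Section {20c} contradicts itself and {20a} on who enters the primary comparison, and nothing elsewhere in the article resolves it. The natural reading is a set selected on attendance after randomisation and labelled intention to treat. This conclusion rests on the wording alone and needs none of the figures above.

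The consequence for the estimate is uncertain in size and direction. Under the assumed inputs it runs from 0 with equal exclusion, through about 0.4 to 0.6 points at 90% against 80% retained, to about 0.7 to 1.2 points at 80% against 60%. The retention rates and the correlation are assumptions, and the document gives no basis for choosing among them.

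**What to change.** Delete the 70% condition from {20c}. State instead that all randomised participants are analysed in the arm assigned, whatever their attendance, that T2 is sought from everyone, including those who stop attending, and that missing T2 values are multiply imputed as already planned.

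If the investigators want a 70% attendance set, name it as a per-protocol sensitivity analysis and say which sessions count. Section {20b} must then be amended, because it now rules out additional analyses.

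Cost: a wording change in {20c}, and in {20b} if the sensitivity set is kept. No extra participants or scheduled visits are needed. There is slightly more imputation work, and the estimate may shift in either direction.
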